#### Concealment mechanism {16b}

The only person who knows the allocation sequence is the research coordinator, who keeps the sequencing on a password-locked computer and only reveals the allocation when the site has sufficient participants to run a group.

### Implementation {16c}

Eight sites are participating to date. The number of sites may increase depending on recruitment speed and funding resources available. Because the sites are geographically and organization-wise spread, the routines for enrollment are adjusted to the routines of the participating sites. The overall strategy is to include as many families as possible who fit the inclusion criteria. Because the sites are organized differently, this goal is reached in slightly different ways for different sites. Some sites send invitations to all families in their databases. Some sites send personal invitations to families known to them. Some sites advertise the trial with posters in waiting rooms. Some sites use a combination of these inclusion ways. Later in the project period, we may also consider advertising the study to patient-user associations and in local media (e.g., newspapers), and we have ethical approval to do so. The advantage of this flexible strategy is that recruitment is faster. The main disadvantages include that we will not be able to calculate an exact response rate, and the feasibility outcomes of the trial may be a bit tricky to interpret. That is, the extent to which our intervention fits “usual care” is more difficult to assess when our enrollment strategy is so flexible.

Across sites, the general procedure principle is that each site coordinator contacts the central project coordinator when they have at least 5 consenting participants. For each intervention group, 3–8 consenting families are required to allocate a randomization number. Participants receive all pre-intervention questionnaires approximately 1 month before the set group date, with regular reminders if not completed. Approximately 2 weeks before the set group date, families and group leaders are informed by the central research coordinator about whether the group was allocated to intervention or waitlist. If assigned to waitlist, participants receive the baseline questionnaires again 2 weeks before the intervention date (approximately 12 weeks after the initial group date). The aim is to conduct 48 groups over the project period. We have pre-generated a randomization list with 100 numbers, ensuring that there will never be more than 3 allocations to the same arm in a row (i.e., intervention or waitlist). This way, the number of participants in both arms will be somewhat balanced if we have to end the trial before reaching our aim of 48 groups, or if we need to increase the number of groups due to < 6 families per group (the aim is 288 families, i.e., 6 × 48).

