**Methods:**

We are conducting a randomized controlled trial comparing a five-session manual-based group intervention for siblings (aged 8 to 16 years) and parents of children with neurodevelopmental disorders to a 12-week waitlist, called SIBS-RCT. The intervention comprises three separate sibling and parent group sessions and two joint sessions in which each sibling talks to their parent alone. The intervention aims at improving parent-child communication and covers themes such as siblings’ understanding of the neurodevelopmental disorder, siblings’ emotions, and perceived family challenges. Participants are recruited through municipal and specialist health centers across Norway. The primary outcome is sibling mental health. Quality of life and family communication are secondary outcomes. Participants are block-randomized to the intervention or 12-week waitlist in groups of six. Measures are collected electronically at pre- and post-intervention/waitlist, as well as 3, 6, and 12 months post-intervention. The main effect to be examined is the difference between the intervention and waitlist at 12 weeks post. All outcomes will also be examined using growth curve analyses. We plan to include 288 siblings and their parents by the end of 2022.

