**Table 2 Tab2:**
[figure not shown]
Schedule of enrollment, interventions, and assessments

*S* siblings, *P* parents, *T* teacher, *O* observer, *C* clinician, *T*^*pre*^ pre-intervention, *T*^*post*^ after intervention/waitlist, *T*^*3m*^ 3 months after intervention, *T*^*6m*^ 6 months after intervention, *T*^*12m*^ 12 months after intervention

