**Fig. 2 Fig2:**

Participant flow chart. T^pre^, pre-intervention; T^post^, immediate post-intervention. T^pw^, post-waitlist; T^3m^, 3 months post; T^6m^, 6 monhts post; T^12m^, 12 month post. *The main group difference to be examined here

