### Statistical methods

#### Statistical methods for primary and secondary outcomes {20a}

The main effect is measured as the difference between the intervention group and the waitlist group in SDQ scores from pre-intervention to 3 months, reported by siblings, parents, and teachers. This is investigated using mixed ANOVA, and effect sizes will be reported as Cohen’s *d*. To examine the effects beyond waitlist for the complete sample, we apply growth curve modeling, which enables us to investigate both mean changes at a group level over time and individual growth trajectories, with the inclusion of individuals with partial/missing data [26]. A series of linear mixed models are fitted. A model with only fixed and random intercepts serves as the null model, to which subsequent unconditional models of time will be compared. Finally, group membership and control variables are included in a set of conditional models, through which the longitudinal effect of the intervention is investigated. Growth curve models are fitted separately for the intent-to-treat sample and per-protocol, excluding participants with concomitant sibling care during follow-up. Multilevel analyses controlling for nesting (group and site level) are conducted with MPlus. Other analyses are conducted using updated versions of IBM SPSS and R.

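### The main contrast has no common time origin, and the stated send dates probably measure the waitlist arm a few weeks earlier than the intervention arm

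*Protocol article*

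**What the plan says.** Two places in the protocol article state the main contrast in words. The abstract (Methods) has "The main effect to be examined is the difference between the intervention and waitlist at 12 weeks post". Statistical methods {20a} has "The main effect is measured as the difference between the intervention group and the waitlist group in SDQ scores from pre-intervention to 3 months", to be tested by mixed ANOVA. The nominal time agrees, but the first counts from an unnamed event and the second can be read as counting from baseline.

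The labels for the waves do not settle it. The Table 2 legend defines Tpost as "after intervention/waitlist", one label for both arms, and T3m as "3 months after intervention". The Fig. 2 legend defines Tpost as "immediate post-intervention", gives the waitlist its own post-waitlist point (Tpw), and attaches an asterisk note, "The main group difference to be examined here". The figure is not shown, so the position of the asterisk cannot be seen.

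The send dates are in Implementation {16c}. Both arms get the pre-intervention questionnaires about a month before the set group date. After allocation to waitlist, "participants receive the baseline questionnaires again 2 weeks before the intervention date (approximately 12 weeks after the initial group date". Sequence generation {16a} has the waitlist receive the intervention after 12 weeks, and Intervention description {11a} puts the two intervention days a week apart.

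**The concern.** A two-occasion group-by-time comparison assumes that the second occasion is the same for both arms. If one arm is measured later, any change in SDQ that would have happened anyway contributes more to that arm's change score, and the difference is counted as treatment effect. Randomisation does not remove this, because the difference in follow-up length is produced by the schedule after allocation.

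The article gives no ground for assuming zero drift: Explanation for the choice of comparators {6b} says that data on how siblings fare over time without intervention are lacking. The trial is also unmasked, so the primary assessment should be fixed before results by arm are seen.

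**Working it through.** **Inputs.** Week 0 is the initial group date. One month is 52.18/12 = 4.35 weeks, so three months is 13.0 weeks.

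- Baseline, both arms: about week −4.35 (Implementation {16c}).
- End of intervention, intervention arm: week 1 (Intervention description {11a}).
- Waitlist intervention date: week 12 (Sequence generation {16a}).
- Target effect: 0.4 SD (Sample size {14}).

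**Waitlist measurement.** If the bracket in {16c} dates the intervention, which fits {16a}, the questionnaire goes out at 12 − 2 = week 10. If it dates the questionnaire, that is week 12.

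**Intervention arm measurement, and gap (intervention minus waitlist, in weeks).**

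| Origin for the intervention arm | Week | Gap, waitlist at week 10 | Gap, waitlist at week 12 |
|---|---|---|---|
| 12 weeks from day 1 | 12 | +2 | 0 |
| 12 weeks from day 2 | 1 + 12 = 13 | +3 | +1 |
| 3 calendar months from day 2 | 1 + 13.0 = 14.0 | +4 | +2 |
| 3 months from baseline | −4.35 + 13.0 = 8.7 | −1.3 | −3.3 |

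Table 2 counts T3m from the intervention and {16a} puts the waitlist intervention at 12 weeks. The most natural combination is therefore week 13 to 14 against week 10, a gap of 3 to 4 weeks. Measured from baseline, that is about 17.3 to 18.4 weeks against 14.3 weeks. Only one combination in the table gives a zero gap, and the article does not state it.

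**Size of the bias.** Bias = gap in months × drift per month.

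- Assumed drift of 0.02 to 0.05 SD per month (not from the article), gap of 3 to 4 weeks: (3/4.35) × 0.02 = 0.014 SD up to (4/4.35) × 0.05 = 0.046 SD. As a share of the target, 0.046/0.4 is about 12%.
- Same drift, gap of 0 to 2 weeks: 0 to (2/4.35) × 0.05 = 0.023 SD.
- Same drift, gap of −1.3 to −3.3 weeks: (1.3/4.35) × 0.02 = 0.006 SD up to (3.3/4.35) × 0.05 = 0.038 SD, with the opposite sign.
- Illustrative upper bound: suppose that the whole mean change of d = 0.43 over six months in the open trial (Background {6a}) were natural and linear. Drift is then 0.43/26.1 = 0.0165 SD per week, and 3 to 4 weeks gives 0.05 to 0.07 SD, or 12 to 17% of 0.4.
- No drift: zero bias for every gap.

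If siblings tend to improve untreated, a later measurement flatters the intervention arm. If they tend to worsen, it penalises it.

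**The case against.** The strongest reply is that this is mostly wording. Twelve weeks and three months name the same nominal time, the send dates are given as approximate, one reading closes the gap altogether, and exact windows belong in the full protocol or analysis plan. Sending the waitlist questionnaire two weeks early also makes sense: many families need several reminders, and the measure must be complete before their first session. Nor do all time-related explanations bear on the gap. Regression to the mean largely affects both arms, and rolling randomisation of groups spreads season across them.

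Much of this stands. It lowers the likely size of the problem and leaves its direction open. It does not remove the problem, because the article itself fixes a waitlist send date that, read naturally, differs from T3m. An analysis plan can name the wave, but it cannot realign questionnaires already sent on different clocks.

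A reader might also infer that the primary time point is defined in three conflicting ways, or that the intervention arm at immediate Tpost (about week 1) is compared with the waitlist at week 10 to 12. That gap would be 9 to 11 weeks, worth about 0.04 to 0.13 SD under the same assumed drift. The visible text does not support this. The Table 2 legend only expands abbreviations and names no primary wave. Only the unseen asterisk could make Tpost the partner of Tpw, and both verbal statements of the main effect point to about three months.

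**Conclusion.** The concern holds in a limited form. The main contrast has no stated common origin, the two legends label Tpost differently, and on the most natural reading the intervention arm is measured 3 to 4 weeks later than the waitlist arm. That gap depends on how the bracket in {16c} and the origin of the three months are read: it may be 0 to 2 weeks, or reversed by about 1 to 3 weeks. Neither the direction nor the presence of bias is therefore established.

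The likely size is about 0 to 0.05 SD under the assumed drift, and about 0.07 SD at the illustrative upper bound, against a target of 0.4. This should be fixed, because the schedule would build arm-dependent follow-up into the primary comparison and the remedy is cheap. It is not a flaw that by itself invalidates the primary analysis.

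**What to change.** Name one primary assessment for both arms, counted from the initial group date, and send the primary SDQ to both arms in the same window. Set that window early enough for waitlist families to finish before their first session. For example, send the intervention arm's SDQ when the waitlist questionnaire goes out, about 2 weeks before the waitlist group date. A window at week 12 itself would leave almost no room before a first session at about week 12.

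Use the same definition in the abstract, the Table 2 and Fig. 2 legends, Implementation {16c} and Statistical methods {20a}, make clear which date the bracket in {16c} refers to, and treat Tpost and the later waves as secondary.

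For families already measured, report actual weeks from the initial group date to SDQ completion by arm, and adjust for them in a sensitivity analysis. That adjustment will be weak if timing varies little within arms, because elapsed time is then nearly the same variable as arm.

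The cost is small. On the week-10 reading, the intervention arm's three-month SDQ moves 3 to 4 weeks earlier. Alternatively, T3m stays where it is and one extra short SDQ is sent; the SDQ-only electronic form described in {18b} already exists. The planned sample size does not change.

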### Assignment of interventions: blinding

#### Who will be blinded {17a}

Masking of participants, assessors, and group leaders is not possible as the control is waitlist and most measures involve self-report. Thus, emergency unmasking procedures are not applicable.

#### Procedure for unblinding if needed {17b}

This is not applicable since masking is not possible.

### Data collection and management

#### Plans for assessment and collection of outcomes {18a}

Primary and secondary outcomes are collected at pre- and post-intervention, plus 3-, 6-, and 12-month follow-up. Participants randomized to waitlist repeat outcome measures after waitlist (see Table 2 for details). While a 12-week waitlist weakens our ability to prove long-term effectiveness of the SIBS intervention, we find it unethical to make vulnerable siblings wait > 12 weeks for an intervention we expect will reduce their symptoms. All questionnaires are collected electronically using “Nettskjema,” an online questionnaire system run by the University of Oslo IT Department. Participants receive a link to the questionnaires via email. The system has built-in features to detect and prevent data entry errors and missing data. To help reduce/prevent dropout, several reminders are sent to participants at every measurement point. If a participant misses a measurement point, they still receive an invitation and reminders at the next measurement point (unless they actively withdraw from the study). Children can respond via their own or their parents’ email address.

#### Plans to promote participant retention and complete follow-up {18b}

Reminders are sent to all participants at each measurement point, via SMS and/or email, depending on participants’ preferences. To collect as much data as possible, a backup electronic version of only the main outcome (SDQ) is offered to participants who do not complete the full questionnaire passages at each measurement point. In cases where participants have not completed the pre-intervention questionnaire before the first group session, time is set apart for the family to complete the main outcome on site.

Newsletters from the project are published twice yearly on the study website (www.sibs.no) to keep participants informed about the study. All analyses will be done with treatment completers as well as the intent-to-treat sample.

See the “Recruitment {15}” section for further details regarding the retention and follow-up plans.

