### Objectives {7}

Objective 1 is to promote sibling well-being by addressing research question 1: *Does the SIBS intervention improve mental health for siblings of children with ND compared to waitlist?* and research question 2: *What are the long-term trajectories of sibling well-being, in terms of mental health, family communication, quality of life, sibling adaptation, and disorder knowledge from pre-intervention to 12-month follow-up?* Based on the findings from our open trial, we hypothesize that the SIBS intervention will outperform waitlist and that the mean 12-month trajectories will indicate significantly improved well-being. Objective 2 is to identify those siblings who are most likely to benefit from the SIBS intervention by addressing research question 3: *Which factors (i.e., ND impairment, parent mental health, family stress) predict outcomes of the SIBS intervention?* Previous findings indicate higher ND impairment and poorer parent mental health will be associated with poorer sibling mental health [1, 3]. However, there is limited knowledge upon which to base hypotheses about predictors of effects. The third research question is therefore exploratory. SIBS-RCT represents a major contribution to the research and practice field towards establishing an evidence-based intervention for siblings. In the event that intervention and waitlist are no different, the impact of SIBS-RCT is still substantial in that we will aim to identify (a) participant subgroups that show positive response and (b) effective components of the SIBS manual, by examining group leader adherence as an outcome predictor. This will allow us to continue to re-engineer SIBS-RCT iteratively to improve outcomes, and avoid promotion of a less-than-optimal intervention.

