#### Methods in analysis to handle protocol non-adherence and any statistical methods to handle missing data {20c}

Manual adherence is included as a predictor of outcomes. We report outcomes from all groups combined, but also examine if outcomes are different if groups with poor manual adherence are removed from the analyses. Our main strategy for handling missing data at the item level is through the default setting of the electronic questionnaires we use—these do not allow missing items. To handle missing data at the participant level, we apply growth curve modeling, which allows the inclusion of individuals with partial/missing data [26].

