## Discussion

SIBS-RCT started participant recruitment and inclusion in September 2019. Recruitment is going according to plan, but many participants need several reminders before completing the online questionnaires. We believe this reflects the strain families of children with ND live under. We developed shorter versions of the questionnaire package to ensure we get as much data as possible on the main outcome variable, the SDQ.

SIBS-RCT corresponds to a societal need, in that Norwegian legislation requires health personnel to address the needs of siblings. Yet, ND and its impact on families represent a global challenge. We have tried the SIBS intervention with 54 families in Cambodia, with promising results on mental health, but not on family communication (submitted). Work is underway to adapt the manual further to the Cambodian culture. The team behind this proposal is interested in further international collaborations, and all materials are translated into English. For requests about implementation, contact the first or last author.

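### The SDQ-only backup form can bias the PCCS, KINDL and NAS trajectories in either direction, and the stated missing-data method makes no use of the SDQ collected at the same wave

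*Protocol article*

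**What the plan says.** All from the protocol article.

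- **Collection schedule** (Plans for assessment and collection of outcomes {18a}): "Primary and secondary outcomes are collected at pre- and post-intervention, plus 3-, 6-, and 12-month follow-up".
- **Backup form** (Plans to promote participant retention and complete follow-up {18b}): "a backup electronic version of only the main outcome (SDQ) is offered to participants who do not complete the full questionnaire passages", and this is done at every wave. For families who have not answered the pre-intervention questionnaire by the first session, "time is set apart for the family to complete the main outcome on site". The short form therefore operates at baseline as well as at follow-up.
- **In use** (Discussion): many participants need several reminders, which the authors believe reflects the strain on these families. In response, "We developed shorter versions of the questionnaire package to ensure we get as much data as possible on the main outcome variable, the SDQ".
- **Missing data** ({20c}): items cannot be skipped in the electronic forms. At participant level, "we apply growth curve modeling, which allows the inclusion of individuals with partial/missing data".
- **Model** ({20a}): a series of linear mixed models, from a random-intercept null model through time to group membership and unnamed control variables. The approach "enables us to investigate both mean changes at a group level over time and individual growth trajectories, with the inclusion of individuals with partial/missing data".
- **Where it is used** (Objectives {7}): research question 2 concerns long-term trajectories "in terms of mental health, family communication, quality of life, sibling adaptation, and disorder knowledge from pre-intervention to 12-month follow-up", with improvement hypothesised.

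**The concern.** Section {20c} deals with skipped items and with participants who have partial data. The short form adds a further pattern: whole instruments missing at a wave the sibling did attend, with the SDQ in hand.

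A likelihood-based growth model of KINDL alone treats a missing KINDL score as ignorable given the sibling's other KINDL scores. If use of the short form also depends on the sibling's current SDQ, and the SDQ is correlated with KINDL, that assumption fails. The variable that would repair it is already in the database.

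The exposure is greatest for research question 2. Waitlist families receive the intervention after 12 weeks (Sequence generation {16a}), so the trajectories to 12 months have no concurrent control in which a missing-data artefact could cancel. A hypothesis of improved mean trajectories could be supported, or masked, by a change over time in who fills in the full package.

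**Working it through.** The plan states no figure on this point, so there is none to reproduce. The check is whether the mechanism works and how large it could be.

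**Assumed inputs (none is in the article).** True change in the secondary outcome is zero. Scores are standard normal, with over-time correlation r = 0.6. The secondary outcome correlates with same-wave SDQ at ρ (absolute value). A share p of responses is SDQ-only, and the probability of the short form follows a logistic rule on current SDQ.

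**Step 1: two waves, baseline complete.** Let δ be the amount, in SD, by which full-package responders have a lower mean SDQ than all siblings. Their secondary score is then better by ρδ at follow-up and, with cross-wave correlation ρr, by ρrδ at baseline. The one-outcome model corrects for the baseline part with slope about r. What remains is

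spurious change ≈ ρδ − r·ρrδ = ρ(1 − r²)δ, with 1 − r² = 0.64.

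| Logit slope | p | δ | ρ = 0.5: 0.32δ | Simulated | ρ = 0.7: 0.448δ | Simulated |
|---|---|---|---|---|---|---|
| 0.5 | 20% | 0.096 | 0.031 | 0.030 | 0.043 | 0.045 |
| 0.5 | 40% | 0.189 | 0.060 | 0.058 | 0.085 | 0.086 |
| 1.0 | 20% | 0.173 | 0.055 | 0.055 | 0.078 | 0.082 |
| 1.0 | 40% | 0.332 | 0.106 | 0.109 | 0.149 | 0.158 |

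δ comes from numerical integration of the logistic rule over a standard normal SDQ. The simulated columns come from 200,000 siblings. Adding SDQ from both waves brings every simulated estimate to within 0.005 SD of zero.

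**Step 2: five waves, varying where the selection occurs.** 20,000 siblings; ρ = 0.3, 0.5 or 0.7; p = 27% or 40%; maximum-likelihood wave means with unstructured covariance. Selection is stronger here: at ρ = 0.5 the raw bias of 0.159 with p = 27% implies δ = 0.159/0.5 = 0.32. Change from baseline to the last wave, in SD (positive = apparent improvement):

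| Short form depends on | Outcome modelled alone | Modelled jointly with SDQ |
|---|---|---|
| Current SDQ, follow-up waves only | +0.05 to +0.19 | −0.01 to +0.01 |
| Current SDQ, share rising by wave | +0.03 to +0.14 | −0.01 to 0.00 |
| Current SDQ, equally at all waves including baseline | −0.01 to +0.01 | −0.01 to +0.01 |
| SDQ at baseline, random later | −0.06 to −0.18 | −0.01 to +0.02 |
| Sibling's own observed baseline score | −0.01 to 0.00 | −0.01 to 0.00 |
| Current, unobserved secondary score | +0.19 to +0.30 | +0.10 to +0.26 |

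**Step 3: reading the table.** Bias appears when selection on SDQ differs between baseline and follow-up, and its sign follows where the selection is stronger. With equal selection, or selection explained by the outcome's own observed history, the one-outcome model is adequate. Joint modelling removes the bias when the SDQ drives the missingness, but only reduces it when the unobserved secondary score does.

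**Benchmark.** The open trial's mean effect was d = 0.43 (Background and rationale {6a}). The range 0.03 to 0.19 is 0.03/0.43 = 7% to 0.19/0.43 = 44% of that.

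**The case against.** The strongest objection is that this is analysis-plan detail. The article does not say that outcomes are fitted one at a time. It neither includes nor excludes the SDQ as an auxiliary variable, and a fuller plan may settle the matter. This stands in part: one-outcome fitting is an inference from the model sequence in {20a}. But {20c} does state a missing-data strategy, and that strategy does not cover the pattern that the trial's own retention procedure produces.

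A reader might go further and infer that quality of life and family communication are bound to appear improved if worse-off siblings get the short form. The documents do not support that. The form is offered at every wave, and the on-site rule at baseline also secures only the main outcome, so selection may be equal across waves (no bias) or stronger at baseline (apparent worsening). Nothing says that short-form use grows with follow-up.

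Three further points against the concern stand:

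- The Discussion speaks of strain on families, not of sibling symptoms. A link between short-form use and the sibling's SDQ is an assumption.
- The form does not itself cause the gap. It goes to people who had not completed the full package, and it supplies the SDQ needed for correction.
- Disorder knowledge (SKI) is a telephone interview (Outcomes {12}), so the form does not displace it.

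The upper ends of the ranges need strong correlation, strong selection and 40% short-form use together. The near-complete correction in step 1 is expected, because missingness there was made to depend on the SDQ alone.

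**Conclusion.** The concern holds in a limited form. PCCS, KINDL and NAS can be missing where the SDQ is present, through non-completion that the authors themselves associate with strain, and the one participant-level remedy named is not said to use that SDQ. If these outcomes are modelled without it, the estimated trajectories may be off in either direction. Under the assumed inputs that means about 0.03 to 0.19 SD of apparent improvement, 0.06 to 0.18 SD of apparent worsening, or nothing, depending on where selection is strongest. Neither direction nor size can be settled from the article, because it gives no short-form share by wave.

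The primary SDQ comparison and SKI are not affected. The change is worth making because research question 2 rests on these uncontrolled trajectories and the correction costs little.

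**What to change.** Keep the short form. In {20a} and {20c}:

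1. Fit the growth models for PCCS, KINDL and NAS with self- and parent-rated SDQ at all waves, baseline included, as auxiliary variables or as a joint outcome. Saturated correlates in Mplus, which the protocol already uses, would do. So would multiple imputation with SDQ from every wave in the imputation model.
2. Report the number and share of SDQ-only responses by wave and arm beside each of these trajectories.
3. Add a not-missing-at-random sensitivity analysis, for example shifting the imputed secondary scores of SDQ-only responders over a stated range, because joint modelling does not remove bias that depends on the unobserved score itself.

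SKI needs no change on this account. The cost is slightly more complex models and some extra reporting, with no new data and no change to the primary analysis.
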